## Abstract

**Introduction:**

Long-term sickness absence represents a major public health challenge with far-reaching consequences for both individuals and society. Musculoskeletal disorders (MSDs) are among the leading causes of sickness absence. Although mobile apps show promise for supporting self-management of MSDs, high-quality evidence remains limited, and outcomes related to work participation are rarely examined. This trial aims to evaluate whether an individually tailored, app-based self-management intervention (SmaRTWork), provided in addition to usual care, improves return-to-work compared with usual care alone among individuals on sick leave due to MSDs.

**Methods and analysis:**

We will conduct a randomised controlled trial with two parallel arms: 1) SmaRTWork in addition to usual care and 2) usual care alone. Individuals 20–59 years old who have been sick-listed for <12 weeks due to back, neck or widespread pain will be recruited through clinicians in primary health care. Eligible participants are randomised 1:1 to one of the two arms. We aim to include 298 participants, 149 in each arm. The primary outcome is time to sustainable return-to-work, defined as one consecutive month without receiving medical benefits, assessed over a 12-month period using registry data. Secondary outcomes include health-related measures assessed at baseline, 3, 6 and 12 months. The trial will also incorporate qualitative studies, a process evaluation and a health economic evaluation.

**Ethics and dissemination:**

The trial is approved by the Committees for Clinical Trials of Pharmaceuticals and Medical Devices (Ref. 563919). Results will be published in peer-reviewed journals and presented at national and international conferences.

**Trial registration:**

NCT07034040.

STRENGTHS AND LIMITATIONS OF THIS STUDYThis study uses a randomised controlled trial design to evaluate the effectiveness of SmaRTWork, an individually tailored, app-based self-management intervention aimed at supporting return-to-work among individuals sick-listed due to musculoskeletal disorders.Qualitative studies and a process evaluation will be conducted to gain insight into participants’ experiences with the SmaRTWork app and to identify key facilitators and barriers to its implementation.A health economic evaluation will be conducted to assess cost-effectiveness, cost-utility and cost-benefit from both healthcare and societal perspectives.A potential selection bias related to technological competence may limit the external validity of the study.Participants are not blinded, only researchers performing the analyses (single-blinded study).

## Introduction

 Long-term sickness absence represents a major public health challenge with far-reaching consequences for both individuals and society.^1
2^ Its negative impact is substantial, including high economic costs, individual suffering and loss of workforce.^2^ Moreover, the literature suggests that sick leave tends to become increasingly complex over time and the likelihood of returning to work decreases as absence is prolonged,^1
3^ indicating that early intervention is likely to be important.

Musculoskeletal disorders (MSDs) are the leading cause of sickness absence in the European Union.^2^ Central in the recommendations for treatment of MSDs is self-management.^4
5^ This approach does not replace the role of clinicians but aims to empower patients, in contrast to earlier models of passive provider-led care.^6
7^ Although definitions vary, self-management generally refers to the ability to cope and manage daily life despite having a chronic condition.^7^ A key element in self-management programmes is to enhance self-efficacy, defined as the “belief in one’s abilities to organize and execute the courses of action required to produce given attainments”.^8^ Accordingly, interventions for MSDs often include education, advice to stay active, exercise and some form of cognitive behavioural therapy.^9^ However, health professionals often lack the time and training to deliver self-management support^10
11^, and adherence to self-management over time can be challenging for many patients without support.^12^ To support self-management and increase adherence, smartphone app-based interventions have emerged as a promising approach during the last decade.^13^ Although some evidence suggests that such interventions may improve self-management of MSDs, the evidence base is limited by few high-quality studies and considerable heterogeneity in intervention content.^14–16^ Moreover, work participation outcomes are rarely examined, and there have been explicit calls for interventions specifically developed for individuals sick-listed due to MSDs.^13–15
17
18^

In a previous randomised controlled trial (RCT), we found that an artificial intelligence-based app (selfBACK) for supporting self-management of low back pain in a primary care setting produced a small, clinically uncertain reduction in pain-related disability.^19^ Another RCT of the selfBACK app was conducted in a specialist care setting without showing an effect.^20^ However, a recent systematic review and meta-analysis found a larger effect on disability than on pain intensity when evaluating digital self-management interventions for low back pain.^14^ This aligns with the aim of self-management, which is to enhance coping rather than to eliminate symptoms.^11^ This is also consistent with the work disability paradigm, which views low back pain as not only a clinical condition but also a psychosocial and work-related issue and that pain relief is not a prerequisite for returning to work.^21^ However, the evidence on the effectiveness of app-based self-management interventions for improving return-to-work among individuals sick-listed due to MSDs remains limited.^14
17^ To prepare this RCT, intervention mapping was used to further develop and refine the selfBACK app to support self-management and facilitate return-to-work for individuals sick-listed due to MSDs.

The primary aim of this RCT is to evaluate whether an individually tailored app-based self-management intervention (SmaRTWork), provided in addition to usual care, improves return-to-work compared with usual care alone among individuals on sick leave due to MSDs. A secondary aim is to evaluate the effectiveness of the SmaRTWork intervention on health-related measures such as pain and sleep. The RCT will also incorporate qualitative studies, a process evaluation and a health economic evaluation.

## Methods

### Trial design

We will conduct an RCT with two parallel arms to evaluate the effectiveness of the SmaRTWork intervention. Additionally, the project includes qualitative studies, a process evaluation and a health economic evaluation. Results will be reported according to the Consolidated Standards of Reporting Trials (CONSORT) statement^22^ and the CONSORT-AI extension,^23^ and this protocol is reported according to the Standard Protocol Items: Recommendations for Interventional Trials (SPIRIT) guidelines^24^ and the SPIRIT-AI extension.^25^ The trial was prospectively registered at ClinicalTrials.gov in June 2025, identifier NCT07034040.

### Eligibility criteria

Potential participants are adults aged 20–59 years living in Norway who have been sick-listed for less than 12 weeks due to back pain, neck pain or widespread pain and who own a smartphone with internet access. The definition of widespread pain was based on the clinical judgement of the referring clinicians. In the study information material, fibromyalgia was given as a typical example.

The following exclusion criteria will be applied: 1) ‘red flags’ indicating possible serious underlying pathology (ie, changes in bladder or bowel function, general feeling of being unwell (malaise), fever and/or unexplained weight loss, reduced muscle (motor) function, sensory loss, walking problems or balance problems, new neck or back pain that started after the age of 55 or feel different from previous pain episodes, pain that does not improve with rest or light activity or pain that is much worse during the night, previous or ongoing cancer, use of steroids/immune-suppressing medications or drug use, pain that is trauma (injury) related) that have not been evaluated by a physician; 2) serious ongoing somatic (eg, unstable heart disease) or mental disorder (eg, psychosis, ongoing manic episode, suicidal ideation) that prevents participation; 3) pain not assessed by a clinician; 4) leg pain that is worse than back pain; 5) unable to take part in exercise/physical activity (eg, use of walking aids, unable to get up and down on the floor independently); 6) current pregnancy; 7) do not have an employer (ie, unemployed or self-employed); 8) insufficient Norwegian language comprehension; 9) sick-listed for more than 3 months in the previous 12 months; 10) a planned return-to-work date within the coming week and 11) previous participation in the trial or concurrent participation in another study that could interfere with the current trial.

### Study context

All legal residents of Norway are covered by the national social insurance system. Medically certified sick leave is covered at 100% for the first 12 months, with some limitations on the size of the salary. The first 16 days are covered by the employer, while the Labor and Welfare Service (Nav) covers the remainder. The employer must, in cooperation with the employee, initiate a follow-up plan before 4 weeks of sick leave and hold a meeting with the sick-listed worker by week 7 of absence. Other stakeholders may be included if relevant. If the employer offers work-related activities or accommodations, the sick-listed worker is expected to participate. Nav has no possibility to sanction the employer if they do not initiate a follow-up plan. Nav is responsible for arranging a meeting with the sick-listed worker and the employer within 26 weeks of sick leave. The sick-listed worker’s general practitioner must attend if requested by the employer or the employee. This is the only mandatory meeting between a sick-listed worker and Nav, and Nav may grant an exemption from holding the meeting. Additional meetings can be held if the sick-listed worker or other stakeholders find it useful.

After 12 months of sick leave, it is possible to apply for long-term medical benefits, work assessment allowance and permanent disability pension, all of which cover about 66% of the original income. Individuals receiving work assessment allowance are expected to work to the extent their work capacity allows.

### Recruitment

Participants are recruited by clinicians that treat MSDs in primary healthcare, that is, general practitioners, chiropractors, physiotherapists and manual therapists. When clinicians identify potential participants based on the inclusion criteria, they provide them with a link or a quick response code to a webpage containing study information and a short screening questionnaire to assess preliminary eligibility (figure 1). Potentially eligible individuals who want to participate submit their contact information to the research team. Final eligibility is assessed by a clinician (physiotherapist, chiropractor or physician) from the research team during a telephone call, which also includes detailed study information and an opportunity to ask questions. If no exclusion criteria apply and the participant wants to continue, they receive a link to the consent form (online supplemental file 3), which is accessed using electronic identification for secure authentication and online signing. Once the consent form is completed, the participant receives an email with a link to the baseline questionnaire. If the questionnaire is not completed within 3 days, a reminder is sent to avoid delays in the enrolment in the trial. A second and final reminder is sent 6 days after the initial email. Participants who consent and complete the questionnaire are randomised to one of the two groups. Figure 1 shows the participant flow. Recruitment for the trial is expected to begin in autumn 2026. Clinicians and participants are recruited nationwide in Norway.

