**ASSESSMENTS:**						
Demographics†		X				
Work type and employment status		X				
Sick leave status		X	X	X	X	X
Factors contributing to sick leave‡		X				
Workability		X	X	X	X	X
Average pain past week		X	X	X	X	X
Worst pain past week		X	X	X	X	
Pain duration		X				
Pain locations		X				
Comorbidity		X				
Health-related quality of life (EQ-5D)		X	X	X	X	
Insomnia symptoms		X	X	X	X	X§
Fear avoidance		X	X	X	X	X§
Pain self-efficacy		X	X	X	X	X§
Brief illness perception		X	X	X	X	
Perceived stress		X	X	X	X	X§
Depressive symptoms		X	X	X	X	X§
Musculoskeletal health		X	X	X	X	
Global perceived effect			X	X	X	
Pain-related function						X
Barriers for self-management						X
Registry data¶						
Qualitative studies					X	

* Weekly responses reported by the participant in the SmaRTWork app. The responses are used to revise the individually tailored self-management plan. Only questions relevant for a given participant (ie, based on baseline information and progress) are included in the weekly reporting.

† Age, gender (man, woman, other gender identity with options non-binary, transgender, intergender, gender questioning, unsure and do not want to answer), height, weight, education (lower secondary school, upper secondary school, vocational school, university/college≤4 years and university/college>4 years), living situation (alone, partner, parents, other adults, young children, older children), work type and employment status.

‡ Challenges related to work accommodations, workplace conflicts, extensive caregiver responsibilities for children, family members or others, financial difficulties and concerns about returning to their current workplace.

§ For the tailoring, only a subset of the items in the questionnaire is used.

¶ Data on use of medical benefits (sick leave, work assessment allowance and disability benefits) and healthcare utilisation (primary and specialist healthcare).

EQ-5D, EuroQol-5 Dimension.

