### Sample size

Sample size calculations based on the results of previous return-to-work interventions^57^ indicate that 149 participants are needed in each group (total 298). The calculation is based on a comparison of return-to-work using survival analysis with a log-rank test with a HR of 0.70 (survival probabilities (ie, no return-to-work) 0.1 and 0.2, alpha 0.05, beta 0.20). There will be no loss to follow-up due to the use of registry data for the primary outcome.

A detailed statistical analysis plan will be developed and uploaded to ClinicalTrials.gov before the randomisation code is unblinded. Time to sustainable return-to-work will be described by cumulative probability curves, and group differences will be assessed by HRs from Cox regression. Absolute and relative differences in the 1-year probability of sustainable return-to-work will be estimated from logistic regression, whereas differences in the probability of working each month during follow-up will be estimated using Poisson regression within a generalised estimating equation model. Differences in the number of sickness absence days at specific follow-up times (3, 6, 9 and 12 months) will be estimated using Poisson regression. Mean group differences in continuous secondary outcomes will be analysed using linear mixed models. The precisions of all estimated effects will be assessed by a 95% CI. All analyses will be performed by the intention-to-treat principle. The statistical model assumptions will be evaluated for all analyses, and if these are violated, alternative modelling approaches will be considered. All analyses will be adjusted for factors that are considered predictors of the outcomes under study (eg, education level) to improve precision. The details will be prespecified in the statistical analysis plan.

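### No stated rule makes randomisation depend on still being sick-listed, and the route from eligibility call to randomisation can outlast the one-week planned-return exclusion

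*Protocol article*

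**What the plan says.** **Order of enrolment (Recruitment).** A web screening questionnaire gives preliminary eligibility. A clinician on the research team then decides final eligibility by telephone. After that call the person receives a consent link, for which no deadline is given. Once consent is signed, the baseline questionnaire goes out by email. A first reminder follows at 3 days, and "A second and final reminder is sent 6 days after the initial email". No closing date for the questionnaire is stated. The condition for randomisation is: "Participants who consent and complete the questionnaire are randomised to one of the two groups".

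**Exclusion of imminent returners (Eligibility criteria, item 10).** The criterion is "a planned return-to-work date within the coming week". It does not say from which date the week is counted.

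**Sick-leave status before randomisation.** Data collection methods lists sick-leave status among the baseline questionnaire items, and the Table 1 row reads "Sick leave status X X X X X", the first mark being baseline. The answer is thus in hand when the person is randomised.

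**Clock and analysis.** The primary outcome is counted over 12 months from randomisation (Outcomes), and all analyses follow intention to treat (Sample size).

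**Planning figures (Sample size).** "149 participants are needed in each group (total 298" are required, with "HR of 0.70 (survival probabilities (ie, no return-to-work) 0.1 and 0.2, alpha 0.05, beta 0.20". No loss to follow-up is allowed for.

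**The concern.** The primary aim concerns people who are on sick leave, and item 10 shows that the investigators want to keep out those about to return anyway. The stated sequence can defeat that intention. Someone whose planned return lies 8 to 10 days after the call passes item 10. If that person takes a day or two over consent and answers the questionnaire after the day-6 reminder, they can be back at work on the day they are randomised.

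Such a person will usually complete the required month off benefits about one month after randomisation, whichever arm they are in. Under intention to treat they stay in the analysis and add events that carry little or no information about the intervention, while the risk set is still nearly complete. The estimated HR moves towards 1 and power falls. The sample size leaves little room for this, because 298 is just the number needed for 80% power.

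**Working it through.** **1. The plan's own figure.** Inputs from Sample size: HR 0.70, no return-to-work 0.1 and 0.2 (read here as intervention and control at 12 months), alpha 0.05 (taken as two-sided), power 0.80, 1:1 allocation.

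- Consistency: ln(0.2)/ln(0.1) = 0.699, so the HR and the two probabilities agree (control relative to intervention).
- Freedman events: (1.960 + 0.842)² × [(1 + 0.70)/(1 − 0.70)]² = 7.849 × 32.11 = 252.04, rounded up to 253.
- Mean event probability: 1 − (0.1 + 0.2)/2 = 0.85.
- N = 253/0.85 = 297.6, that is 298, or 149 per arm. The stated figure is reproduced. Schoenfeld's formula gives 247 events and 247/0.85 = 290.6.

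**2. The timing.** Item 10 covers 7 days. Time from call to randomisation = consent delay (no limit) + questionnaire delay (more than 6 days for anyone who answers after the final reminder). A consent delay of one day is enough to bring the total beyond 7 days.

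**3. A scale for the share affected.** The documents give no share. As a rough guide, take the plan's control-arm probability with a constant hazard:

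- Hazard = −ln(0.2)/12 = 0.134 per month, or 0.134 × 12/52 = 0.031 per week.
- Return in one week = 1 − exp(−0.031) = 3.0%. In two weeks = 1 − exp(−0.062) = 6.0%.
- Of those who pass item 10 at the call, about 3% would return in days 8 to 14. If half of them are randomised only after their return date (an assumption), the share already back is about 1.5%.
- Counting also those due back within a week of randomisation, when randomisation comes 1 to 2 weeks after the call, gives about 3 to 6%.

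The Introduction says that return becomes less likely as absence lengthens, so early rates may be higher, but no figure is given.

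**4. Effect on power and HR.** Log-rank simulation, 149 per arm, 20,000 runs per cell. A share f in each arm has its event at month 1 regardless of arm. All others have exponential event times from month 1, censored at month 12. There are two versions:

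- *A*: 0.1 vs 0.2 applies to those not yet back, so overall non-return is 0.1(1 − f) vs 0.2(1 − f).
- *B*: 0.1 vs 0.2 is held for the whole randomised population.

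| Assumed f | Power, A | Power, B | HR, A | HR, B |
|---|---|---|---|---|
| 0% | 0.81 | 0.81 | 0.70 | 0.70 |
| 1.5% | 0.80 | 0.81 | 0.70 | 0.70 |
| 3% | 0.79 | 0.80 | 0.70 | 0.70 |
| 5% | 0.77 | 0.79 | 0.71 | 0.70 |
| 10% | 0.72 | 0.76 | 0.72 | 0.71 |
| 15% | 0.68 | 0.74 | 0.73 | 0.72 |

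Smaller runs of version A (6,000 per cell) gave 0.82 at 0%, 0.76 at 5% and 0.72 at 10%. In version A the 12-month difference shrinks from 10 points to 10 × (1 − f), for example 9 points at f = 10%.

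**The case against.** - **Status is recorded again before randomisation.** A reader might infer that sick-leave status is looked at only in the telephone call. The documents do not support this: the baseline questionnaire asks for it before randomisation. What stands is narrower: the answer is collected, but no stated rule lets it stop randomisation.
- **The article is condensed.** Figure 1 could not be read here, and the full protocol may contain a re-check or an expiry date for the link. That cannot be excluded. But the article does state its own condition for randomisation, which is consent plus a completed questionnaire. An enrolment gate is also not something that a statistical analysis plan would normally supply.
- **The article limits delay.** The first reminder is there to avoid delays in enrolment, and the second is final. Harm needs both a return date just beyond the week and a late response. This is fair, and it is why the likely share is small.
- **The event is not wholly fixed beforehand.** A reader might say that the outcome of someone already back was decided before allocation. That goes too far: the person can relapse within the month and so not meet the endpoint, and sustaining the return is part of what the trial targets. Giving these people an event at month 1 in every case is therefore a simplification.
- **Larger losses rest on assumed shares.** Shares of 10 to 15% have no support in the documents. Version A also lowers overall non-return below the plan's 0.1 and 0.2; version B, which keeps them, shows smaller losses.
- **Bias.** A reader might infer a biased comparison. The lapse occurs before allocation and affects both arms alike, so the validity of the intention-to-treat comparison is intact.

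**Conclusion.** The gap is real as the article is written: following the stated steps can outlast the one-week exclusion and admit people who are no longer sick-listed. The consequence is dilution and some loss of power, with no bias between arms.

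Its size depends on a share that the documents do not give. On the scale implied by the plan's control-arm probability (about 3% return per week under a constant hazard), an assumed 1.5 to 3% costs at most about 2 to 3 points of power. At 5% the loss is about 2 to 5 points, and at 10% about 5 to 10. The shares above 5% are upper scenarios. The point is a cheap improvement to a stated enrolment rule and does not threaten the trial's conclusions.

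**What to change.** Before recruitment opens (expected autumn 2026):

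1. Make randomisation conditional on the baseline questionnaire's sick-leave answer confirming that the person is still sick-listed.
2. State that the planned-return exclusion (item 10) is assessed at randomisation, so that its week has a reference date.
3. Set a maximum interval from call to randomisation, with a repeat eligibility check if it is exceeded.

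Optionally, prespecify a sensitivity analysis restricted to participants whose registry sick-leave spell was ongoing on the randomisation date. Nav supplies exact spell dates. The status is fixed before allocation, so the restriction does not disturb the randomised comparison.

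The cost is an automatic check on an item already collected (plus a planned-return question if the questionnaire lacks one) and a few sentences in the protocol. A few consented people will not be randomised and must be replaced.
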